## Abstract

Biomarkers of aging, particularly DNA methylation-based clocks, have shown promise as tools to assess whether interventions may impact the rate of biological aging. Among possible interventions physical exercise has shown protective effects against many age-associated diseases, while time-restricted feeding (TRF) has shown metabolic benefits in preclinical models. The combined effect of exercise and TRF on aging biomarkers remains largely unexplored. In this 52-week four-armed, randomized, controlled trial (clinicaltrials.gov: NCT07207044) 240 healthy adults aged 65 and above will be allocated to four groups: combined cardio and strength training (EXE), TRF, combined EXE and TRF, or control. Participants will undergo assessments at baseline, 3, 6, and 12 months, with follow-ups at 2, 5, and 10 years. The primary outcome measure is Dunedin Pace of Aging DNA methylation age with secondary measures including RNA-sequencing, metabolomics, inflammatory markers, microbiome analysis, cognitive and physical measures. By deeply phenotyping participants, the Fasting And eXercise (FAXAge) study will provide novel insights into whether TRF, EXE, or a combination can slow or reverse biological aging in older adults.

## Background

Advances in medicine have among other factors led to an increase in global life expectancy across the twentieth and twenty-first century (Dattani 2023). In combination with declining birth rates, it is projected that by the year 2050, one in every six people worldwide will be above the age of 65 years; in Europe, this number is already one in four people (United Nations 2019). Although increasing life expectancy is positive, aging represents the largest risk factor for developing chronic diseases, and it has been suggested that aging per se should be regarded as a disease (The Lancet Diabetes Endocrinology 2018). Indeed, aging interventions could impact not only lifespan, but also the multitude of diseases associated with old age e.g., type 2 diabetes, cardiovascular disease, and cancer (Barzilai et al. 2016). An approach to impact all these chronic diseases could therefore be to treat aging itself thereby increasing both health- and lifespan.

Impacts of aging interventions in humans can be difficult to assess due to the long lifespan of humans. Efforts to find biomarkers of human aging that can be used to measure effects of human trials have therefore been explored for decades. About a decade ago, it was discovered that human aging tracks closely with changes in DNA methylation and subsequent work on these so-called aging clocks has shown that they are malleable for interventions (Moqri et al. 2023; Justice and Kritchevsky 2020). These biomarkers typically utilize machine learning methods to explore changes in multiple DNA methylation sites that appear to more strongly capture the complex changes in human aging compared to a single biomarker (Horvath and Raj 2018). Importantly, this approach of using machine learning on more complex datasets from physiological to biochemical biomarkers has proven efficacious in capturing the often subtle changes that occur with age, for instance nuclear morphology can be used to predict cell senescence (Teklu et al. 2025), while biological age can be determined by DNA methylation-based aging clocks (Horvath and Raj 2018) as well as portrait photos (Teklu et al. 2025). Based on previous work, we will utilize the Dunedin Pace of Aging DNA methylation clock that has been published to be responsive to cognitive and health-related outcomes (Belsky et al. 2020). Still no consensus has been achieved on the composition of biomarkers for the best model for biological age and little is known about how the different biomarkers relate to each other and to physiological outcomes (Moqri et al. 2023). Prospective intervention studies are therefore needed to establish and validate robust measures of biological age to build on the recent advances in the field (Moqri et al. 2024).

Being physically active is associated with increased life expectancy, potentially by attenuating age-related physiological alterations (American College of Sports Medicine 2009). These include the preservation of a healthier body composition with reduced total and abdominal fat, greater skeletal muscle mass, and higher bone mineral density, as well as improved cardiovascular function, enhanced insulin sensitivity, and lower levels of systemic inflammatory biomarkers (American College of Sports Medicine 2009). Collectively these adaptations contribute to the protective effects of exercise against most chronic age-related diseases (Pedersen and Saltin 2015).

Intermittent fasting and caloric restriction have been shown to increase lifespan in organisms from mice to rhesus monkeys (Willcox et al. 2007; Colman et al. 2009; Francesco et al. 2018) and improve health parameters in humans (Francesco et al. 2018). TRF is a type of intermittent fasting in which no calories are consumed for a period, typically 12–18 h per day. It is currently unknown whether this type of sustainable fasting improves markers of aging in older adults, although data suggests that periods of fasting can be healthy (Francesco et al. 2018). For instance, in rodents, TRF has shown protective effects against metabolic dysfunctions induced by the Western diet such as obesity, cardiovascular disease, hypertension and diabetes (Francesco et al. 2018). These benefits include reduction in body weight, increase in energy expenditure, improved glycemic control, and lower insulin levels, as well as decreases in hepatic fat and hyperglycemia (Francesco et al. 2018). The metabolic protection after TRF has been proposed to be due to metabolic adaptations, characterized by increased amounts of circulating ketones, while fatty acids, glucose and insulin remain at low levels (Francesco et al. 2018). Importantly, TRF has been shown to confer the major lifespan benefit of a calorie-restricted diet in mice (Acosta-Rodríguez et al. 2022). At the cellular level, it is believed that some of the effects of fasting are mediated through the activation of AMP-activated protein kinase (AMPK), recycling of cellular components via autophagy, reduced mTOR activation and increased mitochondrial biogenesis (Francesco et al. 2018). However, loss of muscle and bone mass may limit the use of this intervention in older adults where this could be a serious side effect (Fernández-Rodríguez et al. 2024). Fasting combined with exercise could be a means to mitigate the possible catabolic effect of intermittent fasting (Laurens et al. 2021).

To address these issues, this one-year case–control clinical trial will investigate biological age, as a primary outcome measure using DNA methylation, and secondary outcome measures including physiological and molecular outcomes. Importantly, the study will have a 10-year follow-up period potentially allowing the potential identification of long-term health outcomes. This may allow us to answer the following key questions which are critically needed for the field: 1) Which markers of biological age are clinically relevant? 2) Is biological age amenable for interventions? 3) Which biological age measurement, DNA methylation, omics-based, digital, hematological, physiological or others, is most reproducible? 4) Is biological age predictive of health and future outcomes? 5) Are the non-invasive biomarkers as good as the more invasive biomarkers? 6) How do different biomarkers associate with each other and other health parameters? To answer these questions, a 52 weeks four-armed randomized, controlled intervention trial will be conducted with subjects randomized to either a combined cardio and strength exercise (EXE), fasting via time-restricted feeding (TRF), combined TRF and EXE (FAX), or control group (Fig. 1). This trial will provide new insight into whether TRF and exercise may reduce or potentially reverse the rate of human aging.

**Fig. 1 Fig1:**
[figure not shown]
Overview of the study

We hypothesize that exercise, intermittent fasting and a combination of the two will provide similar, superior benefits to DNA methylation epigenetic age measured with Dunedin Pace of Aging clock (Belsky et al. 2020) when compared to controls after 52 weeks. It is furthermore hypothesized that the interventions will provide similar, superior benefits to CRP, TNF-α, IL-6, IL-8, NAD +, hematologic age, cell senescence in blood smears, cognitive function, transcriptional age (RNA-sequencing), metabolomic changes, microbiome changes, functional age (handgrip strength, gait speed, VO_2_max), body composition, vocal age, and photo age when compared to controls after 52 weeks.

## Methods

### Study design

The study visits will be conducted at the Department of Biomedical Sciences, University of Copenhagen. 240 healthy community-dwelling elderly aged 65 and older in good general health will be recruited and block randomized to either of the interventions for 52 weeks. Assessments are carried out at baseline, 3 months, 6 months, and 12 months and followed up after 2 years, 5 years and 10 years (Fig. 2).

**Fig. 2 Fig2:**
[figure not shown]
Flowchart of the FAXAge experimental set-up

### Participants, recruitment strategy, and randomization

Participants are excluded if they have received another investigational drug or intervention within 1 year, as prior treatments could influence the responses observed in this study, making it difficult to isolate effects to the current intervention. Individuals engaging in more than one hour of systematic strenuous exercise or strength training a week are excluded to maintain similar baseline activity levels across participants and reduce variability in fitness, making the effects of the intervention clearer. Individuals already practicing time-restricted eating are excluded, as they will not show clear pre- and post-intervention responses. We wish to include a representative part of the healthy elderly population; however, we expect significant bias in our data if we only include individuals without chronic diseases. For this reason individuals with severe or dysregulated diseases are excluded, as the disease state may independently impact the intervention outcomes, while allowing one well-managed chronic disease helps limit heterogeneity and risks for the participants. Smoking is an exclusion criterion due to its effects on cardiometabolic health, inflammation, and exercise capacity, all of which could confound study results. Finally, individuals using systemic glucocorticoids, androgens, or antiandrogens are excluded because these medications have strong effects on metabolism, muscle adaptation, appetite, and glucose tolerance, potentially masking or exaggerating the effects of time-restricted feeding and exercise interventions. Participants are recruited via online advertising, on social media, and in the DaneAge Association membership magazine. Participants will be randomized according to a permuted block randomization scheme with a block size of 4, stratified according to biological sex. The randomization list will be generated prior to commencing the study.

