The training protocol is based on the LISA study and guidelines to resistance training of older adults from the American College of Sports Medicine (American College of Sports Medicine 2009; Eriksen et al. 2016). The program is initiated with a 4-week familiarization phase characterized by high-repetition, low-load training, to ensure proper technique, allow musculoskeletal tissue adaptation and to reduce the risk of injury (Signorile 2013). The training period consists of 4 blocks of 13 weeks (the first block includes the 4-week familiarization phase). Each block begins with three sets of 12 repetitions per exercise, with the number of repetitions decreasing in a stepwise manner every three weeks, ultimately concluding with four sets of six repetitions in the last three weeks. Within each block, training will be organized into consecutive 3-week phases during which repetition range, target repetitions in reserve, and number of sets will be maintained constant, allowing sufficient time for adaptation before progressing to the next phase. Load is continuously adapted for each training session based on participant-reported repetitions in reserve in the previous session. When the upper target is reached and maintained for ≥ 2 sessions, load is increased. Target repetitions in reserve vary for each 3-week phase in accordance with the prescribed number of repetitions – the fewer repetitions, the fewer target repetitions in reserve. Every 13th week a deload phase is implemented to facilitate recovery and mitigate fatigue development (Bell et al. 2023). During this week, training volume is reduced ~ 30 to 50% by reducing the number of sets for each exercise and increasing target repetitions in reserve while maintaining the number of repetitions. At the end of each block, an indirect one repetition maximum load test is performed using the Brzycki formula (Brzycki 1993) at a target of six repetitions, to test alignment between participant-reported repetitions in reserve and one repetition maximum based loading to ensure load is progressive (American College of Sports Medicine 2009). After completion of each block, the same progression pattern is repeated in the subsequent block with absolute loads adjusted from the one maximum load test, starting at ~ 65% of calculated one repetition maximum load. Training sessions will be supervised and will take place at the Department of Biomedical Sciences, University of Copenhagen.

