### Statistical considerations

Sample size determination for the interventions trial is conducted using the primary outcome DNA methylation measured at 52 weeks for the pooled three intervention groups (EXE, TRF, FAX) versus the control group (Table 2). Biological age prediction using epigenetics yields a standard deviation of ~10% (Guan et al. 2024). Assuming an expected pooled effect size for the intervention groups versus the control group is considerable (Cohen’s d = 1.0). With a probability of a Type I and Type II error set at α = 0.05 and β = 0.20, respectively, the estimated sample size was 40 participants allocated in a 1:3 ratio (controls:intervention groups). Our 3-month pilot study (Slowage, clinical trials id: NCT05593939) as well as a similar previous 1-year training intervention study with older individuals showed low dropout rates around 5–10% (Gylling et al. 2020). To accommodate the possibility of a higher dropout rate, a total of 240 participants will be recruited whereby 60 participants will be included in each of the four groups (EXE, TRF, FAX, CON), allowing for a 33% dropout rate. Data from dropouts will not be included in the primary outcomes but may be used in exploratory outcomes. Statistical analysis of outcomes will be done blinded by the outcome assessor. For omics-derived statistics, such as DNA methylation and transcriptomics, results will be corrected for multiple comparisons using false discovery rate control, for example Benjamini–Hochberg FDR at 5%.

**Table 2 Tab2:** List of outcomes

Procedure	Baseline	3 months	6 months	1 year	Follow-up (2, 5, 10 years)
DNA methylation (primary)	X	X	X	X	X
Questionnaire	X	X	X	X	X
MoCA	X	X	X	X	X
Height	X	X	X	X	X
Weight	X	X	X	X	X
Body composition	X	X	X	X	X
Blood pressure	X	X	X	X	X
Blood samples	X	X	X	X	X
Microbiome sequencing	X	X	X	X	X
Handgrip strength	X	X	X	X	X
Gait speed	X	X	X	X	X
Seismofit	X	X	X	X	X
VO_2_peak	X	X	X	X	X
Voice recording	X	X	X	X	X
Portrait photo	X	X	X	X	X

It should be noted that, although DNA methylation clocks are among the most established biomarkers of biological aging, they remain surrogate measures that may be influenced by technical variation, tissue source, immune-cell composition, and algorithm selection.

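### A fixed, published block size equal to the number of arms lets anyone in enrolment who knows the earlier allocations in a sex stratum deduce the last allocation of each block

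*Protocol article*

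**What the plan says.** The Participants, recruitment strategy, and randomization section of the protocol article sets a "permuted block randomization scheme with a block size of 4, stratified according to biological sex". It gives one block size and one stratification factor, and adds that "The randomization list will be generated prior to commencing the study".

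The Abstract states that "240 healthy adults aged 65 and above will be allocated to four groups": EXE, TRF, FAX (the combination) and control. Statistical considerations confirms equal allocation, with 60 per arm.

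On location, Study design says "The study visits will be conducted at the Department of Biomedical Sciences, University of Copenhagen", and Interventions says of the resistance training "Training sessions will be supervised and will take place at the Department of Biomedical Sciences, University of Copenhagen". The Retention section adds phone calls every two weeks to participants in all four groups. The only blinding described is of the statistical analysis, under Statistical considerations.

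**The concern.** The block size equals the number of arms, which is the smallest block that equal allocation to four arms permits. Such a block hides least: each allocation in it removes one arm from those still possible, and the last is fixed by the first three.

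This matters where earlier allocations become known at the site. Here a participant is asked to train, to fast, to do both or to do neither, and none of these can be masked after randomisation. Visits and supervised training share one department, so there are only two sequences to follow, one per sex.

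Someone who can foresee the next arm could, knowingly or not, influence who is enrolled next or when. The randomization section describes eligibility in terms that leave some room for judgement, such as whether a chronic disease is severe, dysregulated or well managed. Bias that enters this way alters the composition of the arms. A laboratory outcome and a blinded analysis do not remove it, and baseline adjustment corrects only for what was measured.

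**Working it through.** **Inputs from the protocol article.** Arms: 4, equally allocated. Block size: 4, fixed. Strata: 2 (sex). Total: 240.

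**The plan's own figure.** 240 / 4 = 60 blocks. Each block holds each arm once, so there are 60 × 1 = 60 participants per arm, as stated.

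**Predictability within a block.** There are 4! = 24 possible orders. Listing them gives, for an observer who knows the earlier allocations in the stratum:

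| Position in block | Arms still possible | Chance that the best guess is right |
|---|---|---|
| 1 | 4 | 1/4 |
| 2 | 3 | 1/3 |
| 3 | 2 | 1/2 |
| 4 | 1 | 1 |

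- Certain allocations: one in four, or 25%. With n women and 240 − n men, the count of completed blocks is floor(n/4) + floor((240 − n)/4), which is 59 or 60 for every n.
- Best-guess rate: (1/4 + 1/3 + 1/2 + 1) / 4 = 0.521. Expected correct guesses: 0.521 × 240 = 125, against 0.25 × 240 = 60 by chance.
- Allocations for which control can be ruled out in advance: control has already been used with probability 0, 1/4, 2/4 and 3/4 at positions 1 to 4. The mean is 0.375, or 90 of 240. The sample size is based on the pooled interventions against control, so this bears on that contrast.

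**Effect of varying the block size.** This was simulated with 120 participants per stratum (an assumption, since the sex split is not given). Sizes 4, 8 and 12 were drawn with equal probability. The observer knows which sizes are possible and all earlier allocations in the stratum, and always guesses the arm most probable given that history.

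| Scheme | Certain | Best guess right |
|---|---|---|
| Fixed 4 | 25% | 52% |
| Random 4, 8, 12 | about 3.5% | about 46% |
| Chance | – | 25% |

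**Price in balance.** An unfinished block of size b can leave two arms at most b/4 apart within a stratum. That is 1 for b = 4 and 3 for b = 12; over two strata it is at most 2 and 6 participants respectively.

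**The case against.** The strongest reply is that the risk is conditional. The deduction works only for someone who influences eligibility or timing and also knows the earlier allocations, in order, within the stratum. The article does not say who screens or enrols, or whether participants are randomised singly or in batches. It places visits and training in one department, but it does not say that the same staff recruit, train and test. The term open-label does not appear; it is inferred from the nature of the interventions. All of this stands, and it makes 25% and 52% upper bounds.

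A second reply is that custody of the list and release of allocations may be described in the full protocol. That also stands: their absence from an article is no finding, and preparing the list before the study starts is normal practice. But it does not answer the point, because a perfectly guarded list still gives away the last arm of a block through the allocations already seen.

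A third reply is that varying the block size achieves little, since the best-guess rate falls by only about 6 points. That is fair for average guessability. The material gain is in certainty, which falls from 25% to about 3.5%.

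Three stronger readings are tempting but unsupported. A reader might infer that a quarter of allocations in this trial are in fact known in advance; the article does not show that any enroller has the necessary knowledge. A reader might expect the bias to be worst for FAX against control; nothing in the document supports this. A reader might also suppose that varying sizes remove all certainty; that holds only while the set of possible sizes is unknown to the observer.

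**Conclusion.** The point holds as a weakness in a rule that the article itself fixes. A published block size of 4 for four equal arms makes the last allocation of every block deducible by anyone who knows the earlier ones in that sex stratum. For a fully informed enroller, up to 25% of allocations (59 or 60 of 240) are certain and 52% can be guessed, against 25% by chance.

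The arithmetic is exact. How far it applies depends on whether those who enrol learn earlier allocations. Unmaskable interventions and a shared department make that plausible, but the document does not establish it. It does not show that selection has occurred, and the size of any resulting bias in the methylation outcome cannot be estimated from it. The change is worth making because it is cheap; the point does not show that the trial is compromised.

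**What to change.** For any participants not yet randomised, regenerate the unused part of the list as permuted blocks of randomly varying size within sex, for example 4, 8 and 12. Do not disclose the sizes to site staff, and do not publish them before enrolment ends. A protocol sentence can say that block sizes vary and are withheld, without listing them.

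The cost is a new list and that sentence. Sample size, outcomes and interventions are unchanged. The downside is a slightly larger possible imbalance between arms if a large block is left incomplete.

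The article does not report recruitment status. If randomisation is already complete, report the fixed block size as a limitation and state whether enrolling staff knew earlier allocations.

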### Interventions

Participants randomized to the EXE and FAX group will perform supervised resistance training two times per week as well as cardio training at home two times per week monitored by fitness watches to track heart rate. This combined approach is chosen since both high muscle strength and cardiorespiratory fitness are independently associated with lower all-cause mortality, whereas low levels correlate with increased risk (Schnohr et al. 2025). Accordingly, this intervention is designed to enhance both muscle strength and cardiorespiratory fitness, enabling the investigation of their association with changes in markers of biological age.

The strength training intensity will be individualized and increased over time according to changes in the participant’s training status, aiming to maintain a similar relative load across participants by adjusting loads to a target range of repetitions in reserve. The training program will consist of the same exercises over the 52 weeks and is designed in a progressive manner as this approach has been shown to enable long-term adaptations in muscular strength through progressive increases in mechanical loading and total training stimulus, thereby limiting training plateaus over time (American College of Sports Medicine 2009). It will consist of approximately 1 h of strength training per session with at least 48 h between each session. Participants will perform a standardized, machine-based (Technogym S.p.A, Cesena, Italy) strength training program involving exercises for the lower and upper body. The program includes both multi-joint (leg press, chest press, lateral pulldown and low row) and single-joint (leg extension and lying leg curl) exercises, with an emphasis on multi-joint movements, which have been shown to elicit greater improvements in muscle strength and contribute to improvements in cardiorespiratory fitness compared with single-joint exercises when total training load is matched (Paoli 2017). This effect has been attributed to a higher oxygen demand associated with the involvement of a larger active muscle mass (Paoli 2017).

The training protocol is based on the LISA study and guidelines to resistance training of older adults from the American College of Sports Medicine (American College of Sports Medicine 2009; Eriksen et al. 2016). The program is initiated with a 4-week familiarization phase characterized by high-repetition, low-load training, to ensure proper technique, allow musculoskeletal tissue adaptation and to reduce the risk of injury (Signorile 2013). The training period consists of 4 blocks of 13 weeks (the first block includes the 4-week familiarization phase). Each block begins with three sets of 12 repetitions per exercise, with the number of repetitions decreasing in a stepwise manner every three weeks, ultimately concluding with four sets of six repetitions in the last three weeks. Within each block, training will be organized into consecutive 3-week phases during which repetition range, target repetitions in reserve, and number of sets will be maintained constant, allowing sufficient time for adaptation before progressing to the next phase. Load is continuously adapted for each training session based on participant-reported repetitions in reserve in the previous session. When the upper target is reached and maintained for ≥ 2 sessions, load is increased. Target repetitions in reserve vary for each 3-week phase in accordance with the prescribed number of repetitions – the fewer repetitions, the fewer target repetitions in reserve. Every 13th week a deload phase is implemented to facilitate recovery and mitigate fatigue development (Bell et al. 2023). During this week, training volume is reduced ~ 30 to 50% by reducing the number of sets for each exercise and increasing target repetitions in reserve while maintaining the number of repetitions. At the end of each block, an indirect one repetition maximum load test is performed using the Brzycki formula (Brzycki 1993) at a target of six repetitions, to test alignment between participant-reported repetitions in reserve and one repetition maximum based loading to ensure load is progressive (American College of Sports Medicine 2009). After completion of each block, the same progression pattern is repeated in the subsequent block with absolute loads adjusted from the one maximum load test, starting at ~ 65% of calculated one repetition maximum load. Training sessions will be supervised and will take place at the Department of Biomedical Sciences, University of Copenhagen.

Cardio training will be of self-chosen modality and at moderate to vigorous intensity (> 70% HRmax) since vigorous-intensity exercise may result in greater increases in aerobic capacity than moderate-intensity (Gormley et al. 2008) and that participation in vigorous activities is associated with lower mortality rates (Lee and Paffenbarger 2000). The desired duration will increase from 30 min per session in the first month, 45 min per session in the second month to 60 min per session in the following 3–12 months. Adherence, workout duration, and average and maximal heart rate will be monitored by fitness watches provided to each participant.

Participants randomized to the TRF group will be instructed to abstain from any caloric intake during the targeted fasting window of 16 continuous hours and consume ad libitum during the 8-hour eating window. Participants can choose their preferred eating window and are encouraged to drink plenty of water during fasting. Participants will receive an adherence diary including an eating time log for noting the time of first and last calorie consumption each day.

Participants randomized to the FAX group will be instructed to both exercise and fast during the 52-week intervention.

